# Anti-inflammatory and immune regulatory effects of acupuncture after craniotomy: study protocol for a parallel-group randomized controlled trial

**DOI:** 10.1186/s13063-016-1712-7

**Published:** 2017-01-10

**Keywords:** Craniotomy, Neurosurgery, Acupuncture, Electroacupuncture, Inflammation, Immune function

## Abstract

**Background:**

Despite recent advances in the medical and surgical fields, complications such as infection, pneumonia, or brain swelling may occur after a craniotomy. In some patients, perioperative antibiotic prophylaxis causes adverse effects such as itching, rash, or digestive conditions. Certain patients still develop infections severe enough to require a repeat operation despite antibiotic prophylaxis. Acupuncture has been used to treat inflammatory conditions, and many basic and clinical studies have provided evidence of its anti-inflammatory and immune regulatory effects. The aim of this study is to explore the effects of acupuncture on inflammation and immune function after craniotomy.

**Methods:**

This trial will be a single-center, parallel-group clinical trial. Forty patients who underwent craniotomy for an unruptured aneurysm, facial spasm, or a brain tumor will be allocated to either the study or the control group. The study group will receive conventional management as well as acupuncture, electroacupuncture, and intradermal acupuncture, which will start within 48 h of the craniotomy. The patients will receive a total of six sessions within 8 days. The control group will only receive conventional management. The primary outcome measure will be the C-reactive protein levels, while the secondary outcomes will be the serum erythrocyte sedimentation rate and the tumor necrosis factor-α, interleukin (IL)-1β, and IL-6 levels measured at four different time points: within 48 h prior to the craniotomy and on days 2, 4, and 7 after surgery. The presence of fever and infection, the use of additional antibiotics, the presence of infection, including pneumonia or urinary tract infection, and safety will also be investigated.

**Discussion:**

In this trial, we will observe whether acupuncture has anti-inflammatory and immune regulatory effects after a craniotomy. If our study yields positive results and a placebo-controlled study also finds favorable results following our study, acupuncture could be recommended as an adjunctive therapy after a craniotomy.

**Trial registration:**

ClinicalTrials.gov: NCT02761096. Registered on 27 April 2016.

**Electronic supplementary material:**

The online version of this article (doi:10.1186/s13063-016-1712-7) contains supplementary material, which is available to authorized users.

## Background

A craniotomy is a common surgical procedure performed to remove brain tumors, blood, or arteriovenous malformations (AVM), and to clip an aneurysm, or for microvascular decompression (MVD). Even if the surgery is performed properly, complications, such as infection, pneumonia, or brain swelling, may occur after a craniotomy [1]. Infections are one of the most common postoperative complications, and impairment of immune function after surgery has been shown to be associated with a higher risk of infection as well as other postoperative complications [2]. C-reactive protein (CRP) is an indicator of inflammatory processes and its levels rise in response to surgical procedures or infection. Therefore, it is commonly used as an index of complications after surgery [3–7]. A study that investigated the association between changes in serum proinflammatory and anti-inflammatory cytokine concentrations and postoperative septic complications reported that the postoperative increase in interleukin (IL)-6 concentration was associated with septic morbidity, while an elevated level of the IL-1 receptor antagonist (IL-1ra) was associated with postoperative septic shock [8].

Appropriate antibiotic prophylaxis reduces the incidence of inflammation, although it may cause adverse effects such as itching, rash, digestive problems including diarrhea, or elevation of liver enzyme levels in some patients. Despite recent advances in the medical and surgical fields that have improved postoperative results, certain patients continue to develop severe infections and require a repeat operation, which is associated with increased morbidity and mortality [9, 10]. Therefore, methods that are complementary to conventional postoperative treatment for reducing inflammation and regulating immune function are needed.

Acupuncture has been used to treat a variety of inflammatory conditions including asthma, rhinitis, inflammatory bowel disease, and rheumatoid arthritis. Growing evidence indicates that acupuncture significantly inhibits the inflammatory response [11]. Findings from several clinical studies support the anti-inflammatory effects or immunological functions of acupuncture. Patients with acute pancreatitis, who received 7 days of electroacupuncture, had higher serum IL-10 and lower CRP levels [12]. Based on a systematic review by McDonald et al., reductions in the erythrocyte sedimentation rate (ESR) and CRP levels were observed after patients with rheumatoid arthritis received acupuncture [13]. It has been shown that the anti-inflammatory effects of acupuncture are mediated by downregulation of proinflammatory cytokines such as tumor necrosis factor-alpha (TNF-α), IL-1β, IL-6, and IL-10 [14]. Elevated plasma TNF-α levels in rats exposed to endotoxin decreased after electroacupuncture at *Zusanli* (ST36) [15]. In rats with chronic obstructive pulmonary disease (COPD), TNF-α and IL-1β levels in the bronchoalveolar lavage fluid decreased after electroacupuncture [16]. In rats with spastic cerebral palsy, serum TNF-α, IL-6, CRP, and nitric oxide synthase levels significantly decreased in the acupuncture group [17]. In experimental rats with periodontitis, electroacupuncture was seen to modulate the immune inflammatory response by decreasing the expression of IL-1β and matrix metalloproteinase-8, and increasing IL-6 messenger ribonucleic acid (mRNA) expression [18]. In addition, several studies have been conducted to evaluate the anti-inflammatory effects and regulation of immunity by acupuncture [19, 20].

However, few acupuncture studies focus on its anti-inflammatory effects and effects on immunity in patients who have undergone surgery. In a study with thyroidectomy patients, the plasma CRP levels at the time of surgery and on days 1 and 3 after surgery were remarkably lower in the electroacupuncture group compared to the sham group [21]. In a study of the immune-inflammatory response of patients undergoing supratentorial craniotomy, the levels of IL-10 and IL-8 significantly increased, while the TNF-α, IgM, and IgA levels also changed significantly after electroacupuncture [2]. However, the effects of acupuncture on the anti-inflammatory response after a craniotomy have not been identified. The decrease in the inflammatory response and regulation of immune function are important for rapid recovery from, and prevention of, complications after surgery. The aim of this study is to explore the anti-inflammatory and immune regulatory functions of acupuncture after a craniotomy.

## Methods

This study will be a single-center, parallel-group clinical trial that will be conducted at the Kyung Hee University Hospital at Gangdong, Seoul, Korea. The flow chart of the trial is shown in Fig. 1. The Standard Protocol Items: Recommendations for Interventional Trials (SPIRIT) 2013 Checklist is given in Additional file 1.

**Fig. 1 Fig1:**
[figure not shown]
Study protocol flow chart

### Ethics

The trial will be carried out in accordance with the Declaration of Helsinki and the Korean Good Clinical Practice Guidelines and has been approved by the Ethical Committee of the Kyung Hee University Hospital at Gangdong (KHNMC-OH-IRB 2016-01-005). It has been registered at https://clinicaltrials.gov/ (NCT02761096).

### Participants

#### Subject enrollment and allocation

A total of 40 participants will be recruited for this trial. Patients who underwent a craniotomy for an unruptured aneurysm, facial spasm, or brain tumor are potential candidates for the study. After written informed consent has been obtained, eligible participants will be allocated to the study group or the control group. Patients who agree to receive additional acupuncture treatment will be allocated to the study group, while patients who do not agree will be allocated to the control group.

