#### Inclusion criteria

Participants must meet all of the following criteria in order to be included: (1) planning to undergo regular craniotomy performed for an unruptured aneurysm, facial spasm, or brain tumor, (2) be aged over 18 years, (3) agree to acupuncture treatment that can start within 48 h after the craniotomy, and (4) voluntary participation and provision of a signed Informed Consent Form.

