### Sample size estimation

The primary outcome, the change in serum CRP level from baseline to the second day after surgery, was used to calculate the sample size. Power analysis indicated that a sample size of 16 subjects per group will be required to detect a serum CRP difference of 3.2 mg/dl with a standard deviation of 3.190 with 80% power and a significance level of 5% in a two-tailed (or two-sided) *t* test. We plan to enroll a total of 40 participants with 20 in the study group and 20 in the control group allowing for a 20% withdrawal rate. The sample size was calculated using the followig formula [26]:$$ n=\frac{2{\left({z}_{a/2}+{z}_{\beta}\right)}^2{\sigma}^2}{{\left({\mu}_c-{\mu}_t\right)}^2} $$

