## Discussion

In this study, we aim to explore the possibility that treatment with acupuncture after a craniotomy has anti-inflammatory and immune regulatory effects. Subjects will be assigned to either the study group or the control group on a voluntary basis. If our results suggest efficacy and if a placebo-controlled study also yields favorable results, acupuncture could be recommended as an adjunctive therapy after a craniotomy as it could possibly reduce inflammatory and immune responses after a craniotomy.

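### The title says randomized, but patients choose their own group and the primary CRP test is unadjusted, so a group difference cannot be attributed to acupuncture

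*Protocol article*

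**What the plan says.** The title of the protocol article reads "study protocol for a parallel-group randomized controlled trial". The Methods section opens more cautiously: "This study will be a single-center, parallel-group clinical trial". The abstract likewise does not call the trial randomized.

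The allocation rule is under Subject enrollment and allocation: "Patients who agree to receive additional acupuncture treatment will be allocated to the study group". The same sentence makes those who decline the controls. The Discussion repeats the rule: "Subjects will be assigned to either the study group or the control group on a voluntary basis". No random element is described anywhere.

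Inclusion criteria, item 3, requires that every participant "agree to acupuncture treatment that can start within 48 h after the craniotomy".

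Under Statistical analyses, the primary outcome (CRP change from baseline to the second postoperative day) is compared by a t test or a Mann-Whitney U test, following the per-protocol principle. The sample size section plans "20 in the study group and 20 in the control group".

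**The concern.** A t test at the 5% level has its stated error rate only if the two groups would have had the same expected CRP change without acupuncture. Randomization secures that on average; patient choice does not. The study pools three surgical indications, and willingness to accept needling soon after a craniotomy may be related to indication, extent of surgery or age. Each of these could plausibly affect postoperative CRP.

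Two features of the stated analysis leave this uncorrected. The primary test takes no covariates. The per-protocol set can also move the groups further apart, because the dropout criterion on missed sessions can remove patients only from the acupuncture group.

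At stake is how the result is read. Readers and evidence syntheses that rely on the title would classify the study as randomized and give its CRP difference a causal weight that the design does not support.

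**Working it through.** **1. The design statements side by side**

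| Place | What it implies |
|---|---|
| Title | Randomized |
| Abstract, Methods | Parallel-group clinical trial; randomization not mentioned |
| Subject enrollment and allocation | Group decided by the patient's agreement or refusal |
| Discussion | Assignment voluntary |
| Inclusion criteria, item 3 | All participants agree to acupuncture |

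The title conflicts with two sections that state the same non-random rule. Separately, if every participant must agree to acupuncture, the decliners who are to form the control group do not meet the inclusion criteria.

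**2. The plan's sample size reproduces**

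Inputs from Sample size estimation: difference 3.2 mg/dl, SD 3.190, 80% power, two-sided 5%. With the printed formula:

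n = 2 × (1.960 + 0.842)² × 3.19² / 3.2² = 15.60, rounded up to 16 per group.

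Allowing for 20% withdrawal: 16 / 0.8 = 20 per group, 40 in total. This agrees with the article. The fault lies in the allocation, not in this arithmetic.

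**3. How the planned test responds to an imbalance (illustration)**

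Suppose acupuncture has no effect, but the self-selected groups differ by b mg/dl in expected CRP change. The value of b is an assumption, since the article gives none. With 16 per group:

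- standard error = 3.19 × √(2/16) = 1.128 mg/dl
- noncentrality = b / 1.128, with 30 degrees of freedom
- rejection probability from the noncentral t distribution, two-sided 5%

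| Assumed b (mg/dl) | b / SD | Rejects, 16 per group | Rejects, 20 per group |
|---|---|---|---|
| 0 | 0 | 5.0% | 5.0% |
| 0.8 | 0.25 | 10.6% | 12.1% |
| 1.0 | 0.31 | 13.8% | 16.2% |
| 1.6 | 0.50 | 27.9% | 34.0% |

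**4. The bias can also hide an effect**

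If the true benefit were 3.2 mg/dl and the imbalance ran against acupuncture by 1.6 mg/dl, the apparent difference would be 3.2 − 1.6 = 1.6 mg/dl. The chance of rejection at 16 per group would then be 27.9%, against 78.4% for the same t test without the imbalance.

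**5. More patients do not cure it**

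At b = 1.0 mg/dl with no acupuncture effect, the rejection rate rises from 13.8% at 16 per group to 34.2% at 50 and 59.7% at 100.

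**The case against.** **Safeguards in the plan.** The exclusion criteria remove patients with raised preoperative CRP, steroid or immunosuppressant use, emergency surgery, earlier surgery at the same site and severe medical disease. The statistician is blinded to allocation. The exclusions do narrow some confounding, but they do not balance indication, extent of surgery or age. Blinding the analyst does not make self-selected groups comparable.

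**A fuller plan might adjust.** A journal article condenses its protocol, so covariates might be named elsewhere. But the article does name the primary test, and neither a t test nor a Mann-Whitney U test takes covariates. Nor could a fuller document add randomization without contradicting the allocation rule stated here.

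**Size of bias.** Nothing in the article supports any particular imbalance. This objection stands: the percentages show how the test behaves under an assumption and do not estimate the bias in this study.

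**Stronger readings that the article does not support:**

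- *That self-selection contradicts the planned 20 per group, or will cost power through unequal groups.* An arm can be closed once it has 20 patients. The article does not describe this, but nothing rules it out.
- *That early postoperative recovery drives the choice.* This is possible only if patients choose after surgery. The inclusion criteria and the preoperative baseline sample point to enrolment beforehand, although the allocation section describes candidates as having already had the operation. The timing is unclear.
- *That the authors intend to claim efficacy from this study alone.* The stated aim is exploratory, and the Discussion makes any recommendation conditional on a later placebo-controlled study.

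**Conclusion.** The point holds and must be fixed. The title claims a property that the allocation rule rules out, and the stated primary test does nothing to compensate. As planned, a CRP difference between the groups cannot be attributed to acupuncture.

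The size and direction of any bias are unknown. Under an assumed imbalance of 0.8 to 1.6 mg/dl (25% to 50% of the 3.2 mg/dl target) and no acupuncture effect, the nominal 5% test would reject about 11% to 28% of the time at 16 per group. That range rests on the plan's SD of 3.190 and on the assumed imbalance. The conflict in labelling and the conflict over eligibility rest on no assumption.

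**What to change.** 1. Delete the word randomized from the title and describe the study as a non-randomized, preference-allocated controlled study.
2. Replace the unadjusted primary test with a regression of day-2 CRP (or its change from baseline) on group, adjusted for baseline CRP, surgical indication and age.
3. Report baseline characteristics by group, and limit the conclusion to an adjusted association.
4. Reconcile inclusion criterion 3 with the allocation rule, so that the text says whether patients who decline acupuncture are eligible.

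Items 1, 3 and 4 cost wording and one table. Item 2 needs no extra patients or visits. With three indications the model has 6 parameters (intercept, group, baseline CRP, two indication terms, age), which leaves 32 − 6 = 26 residual degrees of freedom with 32 evaluable patients, against 30 for the t test. Extent of surgery and other unmeasured differences would remain as residual confounding, which is why the conclusion must stay at association.

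Concealed 1:1 randomization of patients willing to accept either group is an alternative only if it covers the whole analysed cohort, or if randomized patients are analysed separately from those who have already chosen. It leaves the planned 16 evaluable and 20 enrolled per group unchanged, but it needs an ethics amendment and loses patients who insist on one group. Recruitment began in May 2016 and was due to end in March 2017, and the article appeared in January 2017. Randomizing only the last patients and pooling them with the rest would leave the comparison confounded, so relabelling with adjustment is the realistic course.

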#### Inclusion criteria

Participants must meet all of the following criteria in order to be included: (1) planning to undergo regular craniotomy performed for an unruptured aneurysm, facial spasm, or brain tumor, (2) be aged over 18 years, (3) agree to acupuncture treatment that can start within 48 h after the craniotomy, and (4) voluntary participation and provision of a signed Informed Consent Form.

#### Exclusion criteria

Participants with any of the following conditions will be excluded: (1) serum CRP level ≥ 1.0 mg/dl before the craniotomy, (2) a condition other than an unruptured aneurysm, facial spasm, or brain tumor as an indication for craniotomy, (3) a craniotomy performed for infectious brain diseases such as brain abscess or subdural empyema, (4) medication use that can affect the immune system or white blood cell (WBC) count, such as immunosuppressive drugs, steroids, or anticancer drugs or use of these medications within 1 month prior to the craniotomy, (5) a history of surgery at the same site, (6) undergoing emergency surgery, (7) a severe medical disease, e.g., congestive heart failure, chronic renal failure or an autoimmune disorder, (8) a pacemaker or an implantable cardioverter defibrillator, or (9) pregnancy.

### Intervention

#### Study group

The subjects in the study group will receive acupuncture treatments in addition to conventional treatment before and after the craniotomy. The conventional treatment involves general management in the Department of Neurosurgery and includes stabilizing vital signs, pain control, perioperative antibiotic prophylaxis, treatment of infections, and other intravenously administered fluid or drug therapy required based on the condition of the patient.

The acupuncture intervention will start no more than 48 h after the craniotomy and will be administered once a day for 6 days (a total of six sessions within 8 days). It will be given in addition to conventional treatments. All interventions will be performed by one Korean Medicine doctor with over 5 years of working experience and a college education of 6 years. This doctor will be trained in the study protocol before the start of the trial.

Acupuncture, electroacupuncture, and intradermal acupuncture will be performed during every session. Sterile disposable stainless steel acupuncture needles (0.25 mm × 30 mm; Dong Bang Acupuncture Inc., Chungnam, Korea) will be used. Acupuncture needles will be inserted bilaterally at the following acupuncture points: LI4, LI11, PC6, ST36, GB39 and LR3, and GV20 [12, 15, 18, 21]. If the GV20 is close to the surgical site, this acupoint may be excluded. After insertion to a depth of approximately 0.5–1.5 cm, the needles will be manually stimulated until *de qi*, which is a subjective experience in which patients feel a radiating sensation considered indicative of effective needling, is achieved.

An electric stimulator (ES-160, ITO Co., Tokyo, Japan) will be connected to the handle of each needle at LI4, LI11, ST36, and LR3 and a current of 5 Hz will be applied. The current intensity will be increased until light muscle contraction is evident and reaches approximately 70% of the bearable intensity. The needles will be left in place for 15 min and then removed. The practitioner will be able to regulate the intensity in response to requests from the patients.

After the needles are removed, intradermal acupuncture needles with tape (DB130A; 0.25 mm × 1.5 mm; Dong Bang Acupuncture Inc., Chungnam, Korea) will be inserted at the same acupoints (LI4, LI11, PC6, ST36, GB39, and LR3 bilaterally, and GV20) and left in place until the next session.

#### Control group

The subjects in the control group will receive conventional treatment alone before and after the craniotomy in the Department of Neurosurgery.

### Assessment

The serum CRP level, ESR, TNF-α, IL-1β, and IL-6 levels will be assessed four times: within 48 h before the surgery, and 2, 4, and 7 days after surgery. A fasting blood sample (8 ml) will be drawn from the brachial vein at a fixed time in the morning before breakfast, centrifuged immediately, and kept in a freezer at −80 °C before the analysis.

Any fever with a body temperature over 38 °C, the use of additional antibiotics, and infections, such as pneumonia or urinary tract infections, will be recorded on the Case Report Form every day during the study period (Fig. 2).

**Fig. 2 Fig2:**
[figure not shown]
The schedule of enrollment, interventions, and assessments

#### Dropout criteria

Participants who meet any of the following criteria will be excluded from the study: (1) more than one session (out of a total of six) missed, (2) need for a repeat operation or other types of surgery, (3) serious neurological deficits that develop after the surgery and significantly worsen level of consciousness and motor skills compared with the preoperative condition, (4) nonconventional antibiotics received immediately after surgery, (5) withdrawal of consent, (6) development of serious adverse reactions and inability to continue the trial, (7) worsening condition whereby it is no longer appropriate for the patient to continue to participate in the study (as decided by the investigator), or (8) a decision by the principal investigator that it is not possible for the patient to participate in the study as planned.

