### Statistical analyses

The statistical analyses will be performed by a researcher who is blinded to the allocation. Following the per-protocol (PP) principle, all the data will be analyzed using SPSS software (version 18.0, SPSS Inc., Chicago, IL, USA) and the results will be presented as mean ± standard deviation (SD) or number (%).

In order to compare the change in serum CRP levels from baseline to the second day after surgery, the average number of days that fever occurred and the number of additional antibiotics used between the two groups, either a *t* test or a Mann-Whitney *U* test will be used. The differences in pre and postoperative blood test results between the two groups will be compared using a generalized linear mixed model (GLMM). To compare events due to infections such as pneumonia, urinary tract infection or other diseases, either the chi^2^-test or the Fisher’s exact test will be used. If the data are not normally distributed, nonparametric methods will be used. Confidence limits of 95% will be calculated, and the results with a *p* value < 0.05 will be considered statistically significant.

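### Excluding patients from the study and analysing all data per protocol can drop the most severe infection cases from the infection, fever and antibiotic comparisons

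*Protocol article*

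**What the plan says.** The Dropout criteria section of the protocol article opens with "Participants who meet any of the following criteria will be excluded from the study". The consequence is therefore removal from the study, not only an end to acupuncture. The criteria that matter here are:

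- criterion 1: more than one of the six sessions missed
- criterion 2: "need for a repeat operation or other types of surgery"
- criterion 4: "nonconventional antibiotics received immediately after surgery"
- criterion 6: "development of serious adverse reactions and inability to continue the trial"
- criterion 7: "worsening condition whereby it is no longer appropriate for the patient to continue to participate in the study", as decided by the investigator

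The Secondary outcome measurement section counts days of fever, antibiotics beyond the conventional postoperative ones, pneumonia, urinary tract infection and other infection. The Assessment section has fever, additional antibiotics and infections entered daily on the Case Report Form. The Safety evaluation section has adverse events entered there too.

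The Statistical analyses section states "Following the per-protocol (PP) principle, all the data will be analyzed using SPSS software". It then names tests for fever days and additional antibiotics, and gives the chi-squared or Fisher's exact test "To compare events due to infections such as pneumonia, urinary tract infection or other diseases". It names no other analysis set.

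The Background gives, as part of the reason for the trial, that "certain patients continue to develop severe infections and require a repeat operation".

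**The concern.** A patient whose infection is bad enough to need another operation has the kind of event the trial is meant to learn about. Under the plan as written, that need is a reason to leave the study, and the per-protocol rule then takes the patient out of the comparison. Worsening judged by the investigator can act in the same way. The infection, fever and antibiotic comparisons would then be made in patients selected partly for not having had the worst course.

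Removal may also be unequal. Only the acupuncture group has sessions to miss, so criterion 1 cannot apply to a control patient. A study patient who is too ill for two sessions is removed, while a control patient in the same state is not, unless another criterion applies. Criterion 7 rests on judgement, and patients choose their own group (Subject enrollment and allocation), so the treating staff know who receives acupuncture.

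What is at stake is the set of clinical outcomes. They are secondary to C-reactive protein, but they are the ones that bear on complications after craniotomy.

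**Working it through.** **1. The plan's own figure, for scale.** The inputs come from Sample size estimation: difference 3.2 mg/dl, SD 3.190, two-sided 5% significance, 80% power.

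n = 2(z for α/2 + z for β)² σ² / (difference)² = 2 × (1.960 + 0.842)² × 3.190² / 3.2² = 15.6, rounded up to 16 per group.

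16 / (1 − 0.20) = 20 per group, 40 in total. The stated figures reproduce. The plan therefore allows for 20 × 0.20 = 4 withdrawals per group, or 8 of 40. The point itself does not depend on this calculation.

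**2. Criteria set against outcomes.**

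- Criterion 2 and infection: the Background itself connects severe infection with a repeat operation, so some infection outcomes can trigger removal.
- Criterion 7 and infection: an infected patient who deteriorates can be removed on judgement. Infection is not named in the criterion, so this is a possible route, not a certain one.
- Criterion 4 and additional antibiotics: criterion 4 is confined to the time directly after surgery, and the outcome carries no such limit. The length of that time is not defined, so the extent of overlap cannot be settled from the text.
- Criterion 6 and safety: both a serious reaction and inability to continue are required. Adverse events are still recorded on the form.
- Not removed by any criterion as such: pneumonia, urinary tract infection, fever, and antibiotics added later.

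**3. Effect of removing event patients.** The documents give no event rates, so every rate below is an assumption. With e event patients among 20, of whom r are removed and nobody else is, the observed rate is (e − r)/(20 − r).

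- Assumed 3/20 = 15.0%. Removing one gives 2/19 = 10.5%. Removing two gives 1/18 = 5.6%.
- Assumed 4/20 = 20%. If all four planned withdrawals had events, 0/16 = 0%.
- Assumed 6/20 = 30%. With the same four removed, 2/16 = 12.5%.

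Over a range of assumed risks p, with a share q of event patients removed, the observed rate is 20p(1 − q) / [20p(1 − q) + 20(1 − p)]:

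| Assumed risk | Half of event patients removed | Three quarters removed |
|---|---|---|
| 10% | 1/19 = 5.3% | 0.5/18.5 = 2.7% |
| 20% | 2/18 = 11.1% | 1/17 = 5.9% |
| 30% | 3/17 = 17.6% | 1.5/15.5 = 9.7% |

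**4. Effect on the comparison.** Suppose both groups truly have 3/20. If two event patients leave one group and none leave the other, the table shows 1/18 against 3/20. That is an apparent difference of 15.0 − 5.6 = 9.4 percentage points where none exists. Equal removal in both groups would lower both rates without creating such a gap.

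**The case against.** Several stronger readings are tempting, and the documents do not support them.

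- A reader might infer that the rules remove infected patients in general. They do not. Infection alone is not a dropout criterion, and milder infections stay in.
- A reader might infer that criterion 4 flatly contradicts the antibiotic outcome. It is limited to the time directly after surgery and can be read as removing patients whose initial regimen was not standard, with later additions counted as outcomes. Acupuncture may start up to 48 h after craniotomy (Intervention, Study group), so some of these prescriptions may precede any session. The wording is unclear, but a contradiction is not shown.
- A reader might infer that the safety summary will leave out patients withdrawn for serious reactions, so that acupuncture looks safer than it is. The Safety evaluation section records any adverse event, grades its severity and relatedness, and sends serious events to the Institutional Review Board. It does not restrict this to completers, and no test for adverse events is listed under Statistical analyses. Omission is possible under the all-data wording, but it is not established.
- Criteria 2, 4 and 6 apply on their face to both groups, so the direction of any bias is not shown.

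It can also be said that a condensed article may leave analysis sets to the full protocol, and that these are secondary outcomes in a 40-patient exploratory trial. The second remark limits the weight of the point. The first does not answer it, because the article is not silent. It states that patients leave the study and that one principle governs all the data. Recording an event on a form also does not place it in a comparison, and nothing says that excluded patients are followed or retained.

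**Conclusion.** The point holds in a bounded form. Following the text as written, patients removed under criterion 2, and possibly under criterion 7, leave the infection, fever and additional-antibiotic comparisons, and these can include the most severe infections. Criterion 1 makes unequal removal possible. Criterion 4 needs clarification against the antibiotic outcome. For criterion 6, loss from safety reporting is a risk and not a finding.

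The size cannot be derived from the documents. The illustrations (15% falling to 10.5% or 5.6%, and 20% falling to 0% in the extreme case) rest on assumed event counts and on removal falling only on event patients. They show that, with 20 per group, one to four removals can largely determine what is seen. They do not predict what will happen. The change should be made, but the conclusion is firm only for the route through repeat operation and the per-protocol rule.

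**What to change.** Change the analysis and follow-up wording only. No treatment, antibiotic or surgical decision needs to change.

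- Analyse fever days, additional antibiotics and infections in all enrolled patients, by group.
- Summarise adverse events in all enrolled patients, and acupuncture-related events in everyone who received at least one session.
- Separate stopping acupuncture from leaving the study. Keep completing the existing daily Case Report Form to the end of the observation period unless consent is withdrawn.
- Report exclusions by group and by criterion.
- Keep the per-protocol analysis as supporting.
- Reconcile Dropout criteria, Secondary outcome measurement, Safety evaluation and Statistical analyses. In particular, define the time limit in criterion 4 and state whether antibiotics given within it count towards the additional-antibiotic outcome.

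The cost is some further form completion for patients who stop early and slightly more analysis work. No new measurement is needed for the event outcomes, since the form already collects them.
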